### **Background**

Recovery following general anaesthesia is a complex issue confounded by the type of surgery, inflammation, different anaesthetic drugs and techniques, patient co-morbidities, and differing patient and clinician perceptions of what constitutes good recovery.

Recovery is not a single entity but rather covers many aspects or domains such as physiological recovery, pain and nausea, emotion and mood, return to normal life or work activities, and cognitive function. It is an entity that is difficult to quantify, which then makes it difficult to study in a systematic manner. For anaesthetists, poor recovery is often relayed by the surgeon days or weeks after the event, and it is usually categorized as an adverse outcome.

Current research tools such as the Aldrete ([1](#_ENREF_1)) or the QoR ([2](#_ENREF_2), [3](#_ENREF_3)) scales, focus on early physiological recovery, or the immediate perioperative period. These recovery scores are not sensitive enough to measure the rate of recovery (change over time), and have not been designed for repeated measures. They are also inadequate to identify poor cognitive recovery.

In 2007, an international group of anaesthetists and neuropsychologists formed an advisory board to create a new quality of recovery scale. The aim was to produce a tool that was simple to perform, but sensitive enough to detect change in multiple domains of recovery over time. The validation experiments have included over 700 patients, and this work has been accepted and is published in Anesthesiology ([4](#_ENREF_4)). It is called the Postoperative Quality Recovery Scale (PQRS). Six domains of recovery are identified: physiological, nociceptive (pain and nausea) emotive (anxiety and depression), functional recovery (return of activities of daily living), self assessed recovery, and cognitive recovery. The scale is completed prior to surgery to provide baseline values, and then repeated at 15 minutes, 40 minutes, 1 and 3 days, and 3 months after the completion of anaesthesia (typically after the last surgical stimulation). Recovery is broadly defined as return to baseline or better.

.

One of the most important benefits of the PQRS scale is that it enables recovery to be quantified and measured. This makes it possible to compare different interventions with the express purpose of developing specific interventions to improve quality of recovery. The PQRS offers a tool to provide the recovery process to be examined. There are no other tools in existence that provide a comprehensive, sensitive assessment of the multiple aspects or domains of recovery, and is yet relatively simple to perform.

Much research has been conducted on the general recovery from knee surgery in relation to mobility and quality of life ([5](#_ENREF_5), [6](#_ENREF_6)) as well as pain relief ([7](#_ENREF_7), [8](#_ENREF_8)) and risk of complications such as deep venous thrombosis ([9](#_ENREF_9), [10](#_ENREF_10)). In addition there has been a significant amount of research that has considered the impact of both hip and knee replacement surgery on cognition where the mechanism of cognitive dysfunction is considered to be lipid microemeboli that have been detected by Trancranial Doppler (TCD) ([11](#_ENREF_11), [12](#_ENREF_12)).

In routine care patients are frequently discharged home on the same day or following day with arthroscopy, which means that they are not assessed by medical or nursing staff until they return for follow-up review, or represent with complications. It is unclear whether long-term recovery (especially cognitive recovery) can be affected by brief surgery such as arthroscopy. The validation data for the PQRS is suggestive that cognitive quality of recovery may be impaired even with brief anaesthesia and surgery.

General anaesthesia induces a reversible but profound state of coma. Recovery from that can vary considerable between individuals as described above. Less is known about the potential contribution from the anaesthetic drugs to the process of complete or incomplete recovery (especially cognitive recovery), largely due to the paucity of randomized trials.

Sevoflurane and desflurane are the two most commonly used anaesthetics in Australia from the “inhalational anaesthetic“ class of drugs. Although they differ in potency, they both produce equivalent depths of anaesthesia. From a pharmacokinetic perspective, desflurane works more quickly than sevoflurane and is eliminated more rapidly as well, leading to more rapid emergence from anaesthesia. Desflurane also undergoes minimal biotransformation (0.02%), whereas sevoflurane undergoes greater biotransformation (5%). In human volunteers undergoing prolonged anaesthesia with either sevoflurane or desflurane, the desflurane group recovered in multiple domains much more rapidly than sevoflurane ([13](#_ENREF_13)). Furthermore, it has been shown that early recovery parameters such as return of pharyngeal reflexes and wakefulness are faster with desflurane ([14](#_ENREF_14), [15](#_ENREF_15)). What is apparent, however, is that there is very little variability in these parameters with desflurane, but considerable variability with sevoflurane leading to a much wider range of recovery times. In the paediatric population, the incidence of emergence agitation is higher with sevoflurane than desflurane([16](#_ENREF_16)). Desflurane, however is more irritant (can lead to coughing) at high concentration, and heart rate can increase if a high concentration is rapidly introduced ([17](#_ENREF_17)). At the typical anaesthetic concentrations used in surgery, however the drugs are comparable in terms of airway irritability and haemodynamic responses ([17](#_ENREF_17), [18](#_ENREF_18)).

It is unknown, however, if there are significant differences in the rate of recovery across the multiple domains that this involves, over a longer time period between these two inhalational anaesthetics, in an adult population when administered for a relatively brief duration.

### **Clinical significance**

Quality of recovery is an emerging field within anaesthesia of great importance. Although large outcome studies are very important in anaesthesia, there is a changing focus from “mortality and morbidity studies”, to quality of recovery. The reason is that the frequency of mortality is now very low with the result that few interventions will further reduce mortality and in any event very large numbers will be required to demonstrate any improvements in surgery and anaesthesia with mortality as an outcome. However early data on the PQRS as well as clinical reports indicate that the quality of recovery is often poor in many patients, and yet these are not identified by the treating anaesthetist. There are implications for the individual patient, for the practice of anaesthesia, and for the community (such as safe return to work or to driving).

Knee arthroscopy is often performed as an outpatient (day) procedure, and therefore may be perceived as “minor surgery”. However, for some patients the quality of recovery including cognitive decline may be more profound than would be expected from brief peripheral surgery. The role of the anaesthetic agent may have an important influence on this recovery. It is frequently assumed by anaesthetists that anaesthetics from the same class should produce similar effects when administered for a brief anaesthetic, but there are insufficient data to validate that assumption. This study will help anaesthetists to choose the anaesthetic that is best for their patients undergoing brief surgery.

Pilot data

At the Epworth Healthcare campuses, we have conducted an observational study investigating the effects of age (young <40 yrs and older >65 years) on recovery in patients having arthroscopy surgery and comparing the older group to knee replacement surgery (HREC # 46309). To reduce the risk of confounding bias, all patients received the same anaesthetic (desflurane).

However, we conducted a pilot study arm with sevoflurane as the general anaesthetic agent. We recruited 10 patients in each of the young and older cohorts. Other aspects of the study conduct were identical to the patients receiving desflurane anaesthesia. In brief, Patients were induced with propofol, and maintained on wither desflurane or sevoflurane according to allocation. Intraoperative and postoperative opiates were used for analgesia. Nitrous oxide anaesthesia was not used. Patients were typically discharge on the same day of surgery. PQRS measurements were performed at Baseline n the day of surgery, 15 and 40 minutes, 1 and 3 days, and 3 months after the end of anaesthesia.

Pilot study results:

Due to the small numbers in each of the young and old groups in the sevoflurane arms, all patients were combined to compare the recovery profiles of desflurane and sevoflurane. However, the proportion of patients in young and old ages were the same for both anaesthetics. 122 patients are included in the desflurane group and 20 in the sevoflurane group.

The figure below shows recovery between groups for all domains, as well as the individual recovery domains.

The P value displayed is derived using the Cochran Mantel Haenzel test for repeated

measurement of proportions, and tests the global hypothesis of whether a difference exists in the recovery profiles over time between the two agents. P<0.05 was used to define significance.

Caution must be exercised in interpreting the P value, due to the small n in the sevofluane group compared to the desflurane, and there is high chance of Type II error where there is a P>0.05. Rather, place emphasis on the presence of absence of differences in the recovery profiles, as an indicator of effect size.

*A. Physiological recovery domain for Time 15 and 40 minutes. B. Cognitive recovery profile using the revised cognition scoring method. C. Nociceptive domain includes pain and nausea. D. ADL is activities of daily living and tests the ability to eat, walk, stand and dress. E. Emotive recovery tests feelings of anxiety and depression. F. Overall recovery is present when there is recovery on all of the domains (A-E).*

Of note, there is improved nociceptive recovery with desflurane (P<0.05). All other domains were not statistically different, but there were reasonable effect size differences for Cognitive recovery on day 1 (desflurane 78% vs sevoflurane 56%), and for all domains recovery on day 3 (desflurane 35.2% vs sevoflurane 20%).

### **Objectives:**

1. To identify whether the rate/quality of recovery is affected by sevoflurane versus desflurane when used as the primary anaesthetic for knee arthroscopy surgery.

### **Hypothesis**

1. The null hypothesis is that there is no difference in recovery measured using the PQRS, in patients undergoing knee arthroscopy under general anaesthesia with either sevoflurane or desflurane as the primary anaesthetic.

### **Study design**

Parallel randomized trial with allocation ration 1:1.

### **Study environment**

The study will be conducted in a multi site private hospital, which has an active orthopaedic unit (Epworth HealthCare Richmond or Box Hill, Victoria, Australia). It is anticipated that a 24 month study period will be required. The institution conducts approximately 1500 orthopaedic operations per year, of which knee surgery constitutes approximately 25% of operations. The patient cohort is selected so as not to compete for patients with a current study, as well as to control for age.

### **Eligibility criteria**

Inclusion:

1. Adult patients undergoing knee arthroscopy surgery under general anaesthesia

Exclusion:

1. Patients, who are not fluent in English, will be excluded, as they may be unable to answer the recovery questionnaire adequately.
2. Patients undergoing regional anaesthesia only

### **Interventions**

**Common management for both groups wil include the following:**

1. Pre-medication other than oral analgesic (such as paracetamol) will not be used.

2. Induction will be with intravenous propofol, including co-induction consisting of fentanyl 25-100 micrograms and midazolam 1-5 mg. Antimemetics including dexamethasone and 5HT_3_ antagnists (such as ondensetron) may be administered by the treating anaesthetist.

3. Analgesia will consist of intraoperative opiates, 1 g paracetamol qid, intravenous opiates during early recovery (such as 1.v. fentanyl), Morphine 2.5-10mg sc 3 hourly, or oxynorm 10-20mg 6 hourly will be used for breakthrough analgesia. NSAID’s including Cox II inhibitors (such as paracoxib 40mg i.v. amy be used.

4. Patients will not be included in the study if the treating anaesthetist considers that a regional anaesthetic rather than a general anaesthetic would be in the best interest of the patient. This would most likely be a spinal anaesthetic.

**Intervention drug.**

Following induction of general anaesthesia either desflurane or sevoflurane will be introduced as the maintenance anaesthetic and titrated to maintain an adequate clinical depth of anaesthesia for the remainder of the operation. Typically this will involve anaesthetic concentrations of 6% desflurane and 2.4% sevoflurane, reflecting the different potencies of the drugs. If Bispectral index monitoring (depth of anaesthesia monitor) is available, the target range is 40-60.

### **Outcome measurements for both studies**

**Primary outcome**:

Quality of recovery, as measured by the postoperative quality recovery scale (PQRS) at Day 3 for recovery in all of the individual recovery domains (all domains recovery).

**Secondary outcome**:

1. Recovery for all domains and within domains at the other time points of measurement (15 minutes, 40 minutes 1 day, 3 days and 3 months following cessation of anaesthesia). The domains of recovery are physiological, nociceptive, emotive activities of daily living, cognitive and overall patient perspective.

**Study assessments protocol**

Patients will be recruited prior to but on the same day as surgery. Baseline measurements using the PQRS will be performed prior to premedication.

Measurements will then be performed using the PQRS battery at 15 minutes, 40 minutes, one day, three days and three months following surgery. This is the same testing paradigm as we have used in the validation study of the PQRS. Whilst in hospital, testing will be conducted face-to-face, whereas following discharge from hospital; these will be conducted via telephone interview.

### **Study size**

Sample-size estimates are based on the pilot data for all domains recovery at day 3 (desflurane 35.2% vs sevoflurane 20%) and using Fisher’s exact method to determine a difference of 10% difference in the total score using a 2-tailed test with 80% power at a *P*=0.05 significance. The minimal sample size is 137 for each group. This will be increased to 150 patients per group to account for potential non-completions.

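### The Study size paragraph claims 80% power for a 10% difference in a total score, but 137 per group fits the 15.2-point pilot difference in a yes/no endpoint, and Fisher power for 10 points is about 39–47% at pilot-anchored rates

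*Protocol*

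**What the plan says.** The Study size section opens with "Sample-size estimates are based on the pilot data for all domains recovery at day 3 (desflurane 35.2% vs sevoflurane 20" per cent), which is a difference of 15.2 percentage points in a proportion. The same sentence names Fisher's exact method and gives the purpose as "to determine a difference of 10% difference in the total score using a 2-tailed test with 80% power" at a significance level of 0.05. It arrives at a minimum of 137 per group, raised to 150 to cover non-completion.

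The Primary outcome section defines the endpoint as the PQRS result "at Day 3 for recovery in all of the individual recovery domains (all domains recovery"). The figure note under Pilot data says that overall recovery is present when there is recovery on every domain, so each patient either has it or does not. The Statistical methods section assigns Fisher's exact test to the primary endpoint. The Study design section reads "Parallel randomized trial with allocation ration 1:1". The protocol defines no PQRS total score as an endpoint.

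**The concern.** One sentence sets two sizing targets that differ in size (15.2 against 10) and in kind (a proportion against a score). At most one of them can be what 137 per group delivers at 80% power.

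What is at stake is the power claim for the primary endpoint. Taken at its word, the sentence says that a 10-point difference would be found four times in five. If that is false, a non-significant result could be read as evidence against a difference of that size when the trial had no good chance of seeing it. A true difference below 15.2 points is a realistic prospect: the sevoflurane pilot arm had 20 patients, and the protocol's own pilot section urges caution because of that small number.

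**Working it through.** **Inputs.** From Study size: rates 35.2% and 20%, two-sided test, 80% power, significance level 0.05, 137 per group raised to 150, Fisher's exact method. From Study design: 1:1 allocation. From Statistical methods: Fisher's exact test for the primary endpoint.

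**Step 1: reproduce 137.** Uncorrected normal approximation with pooled variance under the null, where p̄ is the mean of the two rates:

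n per group = { [1.96·√(2p̄(1−p̄)) + 0.8416·√(p₁(1−p₁) + p₂(1−p₂))] / (p₁ − p₂) }²

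For 35.2% vs 20%, p̄ = 0.276. The two terms are 1.2390 and 0.5243, so n = (1.7634 / 0.152)² = 134.6, or 135. Variants for the same pair:
- unpooled variance: 132
- arcsine: 134
- continuity correction: 148
- rates rounded to 35% vs 20%, pooled formula: 138

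The stated 137 is therefore approximately the 15.2-point calculation without correction.

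**Step 2: try the 10-point target.** The protocol gives no pair of rates 10 points apart, so a pair must be assumed. The first two pairs below each keep one pilot rate and bring the other to within 10 points of it. The third places the difference below the pilot sevoflurane rate.

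| Assumed rates | n per group, pooled | With continuity correction | One-sided, pooled |
| --- | --- | --- | --- |
| 30% vs 20% | 294 | 313 | 231 |
| 35.2% vs 25.2% | 330 | 350 | 260 |
| 20% vs 10% | 199 | 219 | 157 |

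For the first row, (1.2002 + 0.5119) / 0.10 = 17.12, and its square is 293.2, or 294. None of these gives 137.

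**Step 3: power under the named test.** For each pair of counts (x₁, x₂), compute the two-sided Fisher P value. Power is the sum of Bin(x₁; n, p₁)·Bin(x₂; n, p₂) over all pairs with P ≤ 0.05.

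| Assumed rates | Difference | 137 per group | 150 per group |
| --- | --- | --- | --- |
| 35.2% vs 20% | 15.2 points | 77.2% | 81.3% |
| 30% vs 20% | 10 points | 42.8% | 46.9% |
| 35.2% vs 25.2% | 10 points | 38.8% | 42.5% |
| 20% vs 10% | 10 points | 58.9% | 62.9% |

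The pooled normal approximation is kinder but leads to the same conclusion. At 137 and 150 it gives 48.0% and 51.6% for 30% vs 20%, 43.7% and 47.0% for 35.2% vs 25.2%, and 64.1% and 68.1% for 20% vs 10%.

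**Step 4: what Fisher's test would need.** For 35.2% vs 20%, power is 79.5% at 145 per group, first reaches 80% at 147, and is 80.6% at 148. For 10 points it takes about 312 per group (30% vs 20%) or 348 (35.2% vs 25.2%).

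**Step 5: the allowance for losses.** The increase is 150 − 137 = 13 per group, or 13/150 = 8.7%. Under Fisher's test, power for 15.2 points stays at 80% or more only while at least 147 per group complete, that is, with no more than 150 − 147 = 3 lost per group. If all 13 are lost, power is about 77%.

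**The case against.** The best defence is that the 10% phrase is a wording leftover. The rates used are printed in the same sentence, the endpoint and test are clear elsewhere, and 137 follows approximately from those rates. The phrase drives no number: endpoint, enrolment and analysis are the same without it. The words about a total score may be a loose name for the all-domains composite. Much of this stands, and it is why the remedy is a rewording. It does not rescue the sentence, which states a detectable difference and a power that do not belong together.

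A second objection is that power for 10 points depends on assumed rates. That is right, so the figure is given as a range with its rates. Saying that such a difference would be missed more often than found holds for the two pilot-anchored pairs under Fisher's test but not for 20% vs 10%. Rates well below the pilot's would raise power further, but nothing in the protocol points to them.

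A reader might also infer three stronger things that the document does not support:
- **That the trial is too small and should have roughly 300 or more per group.** This would follow only if 10 points were the intended target. The protocol nowhere justifies 10 points as a clinically important difference, and its sample size follows the pilot rates.
- **That a different, continuous primary endpoint was planned.** The Primary outcome and Statistical methods sections both point to a proportion.
- **That removing the 10% phrase leaves a correct statement of 80% power at 137.** It does not: under the named test, 137 gives about 77% for 15.2 points.

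**Conclusion.** The sentence is wrong as written. The sample size corresponds to 35.2% vs 20%, and the claim of 80% power for a 10-point difference fails under every pair of rates tried. Fisher power at 137–150 per group is about 39–47% when either pilot rate is kept, and 59–63% for 20% vs 10%. If the 10% was meant as a relative difference, the absolute difference is smaller and power lower still.

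The second, smaller error is that 137 per group is an uncorrected normal-approximation figure presented as a Fisher calculation. For the pilot difference itself, Fisher power is about 77% at 137 and about 81% at 150 with no losses.

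The 15.2-point figures rest only on the protocol's own inputs. The 10-point figures rest also on the assumed rates shown.

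**What to change.** In the Study size section:

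1. Delete the clause about a 10% difference in the total score.
2. State that the trial is sized on 35.2% vs 20%, a difference of 15.2 percentage points, in the proportion of patients with all-domains recovery at Day 3.
3. Restate the power under two-sided Fisher's exact test at the 0.05 level: about 77% with 137 completers per group and about 81% with 150 per group.
4. Add that power for a 10-point difference is only about 39–47% at the pilot-anchored rates (30% vs 20% or 35.2% vs 25.2%), so a non-significant result does not exclude a difference of that size.

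The sponsor should confirm which target was meant. If it was 10 points, the stated 80% must be replaced by the lower figure with its assumed rates.

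The cost is a rewritten sentence or two and a less favourable statement of power. It needs no extra patients and no change to the endpoint or the primary test.

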### **Statistical methods**

Continuous variables will be analysed by Student’s t test for independent samples, or repeated measures ANOVA for multiple measurements over time. The primary endpoint will be assessed using Fisher’s exact test. Recovery profiles over time will be tested using the Cochran Mantel Haenzel test for repeated measurement of proportions, and will test the global hypothesis for difference between groups over time.

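### The stated minimum of 137 per group does not reproduce under Fisher's exact test, which needs 147 for 35.2% vs 20%; 150 enrolled then leaves room for about 3 losses per group at day 3, not 13

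*Protocol*

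**What the plan says.** The Study size section of the Protocol starts from pilot rates of all-domains recovery at day 3: 35.2% with desflurane and 20% with sevoflurane. It describes the calculation as "using Fisher’s exact method to determine a difference of 10% difference in the total score", "using a 2-tailed test with 80% power" and "0.05 significance". The result is "The minimal sample size is 137 for each group. This will be increased to 150 patients per group to account for potential non-completions". No expected rate of non-completion is given, and no visit to which it would apply.

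Study design fixes equal allocation ("Parallel randomized trial with allocation ration 1:1"). Primary outcome makes the endpoint binary at day 3: recovered in all domains or not. Statistical methods says "The primary endpoint will be assessed using Fisher’s exact test". The test named for sizing and the test named for analysis therefore agree.

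**The concern.** Fisher's exact test is conservative. At 150 per group its true two-sided size is about 3.6% to 3.8% for common recovery rates between 20% and 35.2%, not 5%. It therefore needs more patients than an uncorrected comparison of two proportions. A figure of 137 looked low for a 15.2-point difference under that test.

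What is at stake is the meaning of the margin. Enrolment was raised above the minimum solely to absorb non-completions. If the true minimum is higher, part of that margin is already used to reach 80% power, and anyone monitoring completeness against 137 would be watching the wrong threshold.

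**Working it through.** **Inputs.** Rates p1 = 0.352 and p2 = 0.20, two-sided alpha 0.05, power 80%, minimum 137 and enrolment 150 per group (Study size); 1:1 allocation (Study design); Fisher's exact test for the primary endpoint (Statistical methods). The difference is d = 0.352 − 0.20 = 0.152.

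**Step 1: reproduce the plan's figure by the method it names.** For n per group, sum Bin(x1; n, 0.352) × Bin(x2; n, 0.20) over all pairs (x1, x2) for which the two-sided Fisher P value is at most 0.05. Defining the P value by minimum likelihood or by doubling the smaller tail gives the same power at every n from 130 to 155.

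| n per group | Fisher power |
|---|---|
| 137 | 77.2% |
| 146 | 79.9% |
| 147 | 80.2% |
| 150 | 81.3% |

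The first n to reach 80% is 147, and power stays at or above 80% at every n from 147 to 165. The stated 137 does not reproduce.

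**Step 2: cross-check by formula.** The mean rate is (0.352 + 0.20)/2 = 0.276.

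- Uncorrected, pooled: n = [1.960 × √(2 × 0.276 × 0.724) + 0.842 × √(0.352 × 0.648 + 0.20 × 0.80)]² / 0.152² = (1.239 + 0.524)² / 0.0231 = 134.6, so 135.
- With continuity correction, the usual approximation to Fisher: n = (134.6/4) × [1 + √(1 + 4/(134.6 × 0.152))]² = 147.4, so 148.
- Arcsine: 133.4, so 134. Unpooled: 131.8, so 132.

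The corrected formula agrees with the enumeration to within one patient. The stated 137 lies nearer the uncorrected figures.

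**Step 3: does rounding of the pilot rate matter?** The pilot had 122 desflurane patients, and 43/122 = 35.2%. With 43/122 vs 20%, Fisher needs 146 and power at 137 is 77.4%. With 35% vs 20%, power at 137 is 76.1% and 80% is first reached at 150. Rounding does not rescue 137.

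**Step 4: the margin at 150 enrolled.**

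- Against 137: 150 − 137 = 13 per group, and 13/150 = 8.7%.
- Against 147: 150 − 147 = 3 per group, and 3/150 = 2.0%.

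**Step 5: the other difference in the same sentence.** The 10% difference cannot explain 137 either. For 10 points, Fisher power at 137 is about 39% (35.2% vs 25.2%) to 43% (30% vs 20%), and the continuity-corrected formula asks for 350 or 313 per group respectively. Only 35.2% vs 20% brings the required number near 137.

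**The case against.** **The consequence is small.** The trial enrols 150 per group, which gives 81.3% under the plan's own test and rates. With 13 lost per group the shortfall is 80 − 77.2 = 2.8 points. Type I error and the endpoint are unaffected. This stands, and it sets the severity.

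**The loss of 13 per group is inferred.** The plan states no loss rate. The increase may be meant to cover the 3-month assessment, and losses by day 3 cannot exceed losses by 3 months. This also stands: 77% is a conditional figure, not the power the plan implies it will have.

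**The inputs are softer than the gap.** The 20% comes from 20 sevoflurane patients. If that is 4/20, the exact 95% interval is about 6% to 44%. Moving the desflurane rate from 35% to 36% moves Fisher power at 137 from 76% to 81%. This is true, but it bears on how far the pilot rates can be trusted. It does not make 137 the correct result for the rates, test and power that the section states.

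**The sentence has a larger problem.** The gap between 10 and 15.2 points matters far more than that between 137 and 147. This stands, and means that 147 should be quoted only together with the difference it belongs to.

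A reader might also infer that 137 came from an uncorrected chi-square formula mislabelled as Fisher. The document does not show this: with 35.2% those formulas give 132 to 136, near 137 but not equal to it. The origin of the figure is unknown, and the point does not depend on it.

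**Conclusion.** The arithmetic point holds. For 35.2% vs 20%, two-sided 0.05 and 80% power, the named test needs 147 per group, 10 more than stated. The increase to 150 leaves about 3 losses per group (2%) at day 3 before power falls below 80%, not 13 (8.7%).

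A reader might go further and conclude that the trial is underpowered or must be enlarged. The documents do not support that on these rates, because 150 completers per group exceed 80%, and nothing says that 13 per group will be missing at day 3. It is a modest correction, not one on which the trial's validity turns.

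The conclusion assumes that 35.2% vs 20% is the intended design effect and that the primary analysis is the unadjusted two-sided Fisher test as written. If a 10-point difference is the true target, neither 137 nor 147 is adequate and the calculation must be redone.

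**What to change.** In Study size, replace the sentences giving the minimum and the increase with wording such as:

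*For 35.2% vs 20%, Fisher's exact test (two-sided 0.05) needs 147 per group for 80% power. Enrolling 150 per group allows about 2% non-completion at day 3; 137 completers per group would give about 77% power.*

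In the same edit, reconcile the 10% difference with the 15.2 points used here, stating one target difference and the pair of rates it refers to.

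On the 15.2-point reading, this costs a few sentences in one section, with no extra patients and no change to the primary test.
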